### 2.6. Endpoints

Primary endpoint

Post-operative pain: measured using a 10-point visual analogue scale completed by the participant prior to discharge following TPPB. This is approximately 3–4 h post general anaesthesia, reflecting standard hospital protocols, resulting in a consistent and comparable timeframe across study participants.

Secondary endpoints

Post-operative analgesia requirements, recorded as type, route, and dose, converted to oral morphine equivalentRate and severity of complications arising from use of PPNBProcedure duration and number of biopsy cores obtained

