## 2. Patient and Methods

### 2.1. Study Design

This is a prospective, multicentre, randomised controlled trial (RCT) designed to evaluate the efficacy of PPNB in men undergoing TPPB under general anaesthesia. Participants will be recruited from three centres in Sydney, Australia: Chris O’Brien Lifehouse, Sydney Adventist Hospital, and Blacktown District Hospital.

The primary objective of this trial is to determine whether the addition of a periprostatic nerve block reduces post-operative pain, measured using a 10-point visual analogue scale (VAS) prior to discharge, in men undergoing transperineal prostate biopsy under general anaesthesia.

The secondary objectives are to evaluate whether the use of a periprostatic nerve block is associated with differences in complication rates compared to placebo, and to assess whether it reduces the requirement for post-operative analgesia.

This study has received ethical approval from the Sydney Local Health District Human Research Ethics Committee (2020/ETH03024) and has been registered with the Australian New Zealand Clinical Trials Registry (ACTRN12621001143819). All procedures will be performed in accordance with the National Statement on Ethical Conduct in Human Research (2018), Good Clinical Practice guidelines, and the principles of the Declaration of Helsinki. Trial conduct will be overseen by the principal investigator at each site, with central coordination by the chief investigator and support from a study coordinator.

At the study conclusion, a formal data analysis will be undertaken to obtain the result of this study. A schematic SPIRIT format of the study design is outlined in Table 1.

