### 2.5. Intervention

All enrolled participants will undergo TPPB under general anaesthesia and will be randomised as outlined earlier. Immediately prior to biopsy, patients will undergo a periprostatic nerve block (intervention arm) or a placebo injection (control arm).

The PPNB will be performed under ultrasound guidance using a spinal needle advanced transperineally to the space between the prostate and seminal vesicles, targeting the neurovascular bundles bilaterally. A total of 20 mL of 1% lignocaine with adrenaline will be administered (10 mL on each side), with local anaesthetic visualised during injection to confirm placement and minimise risk of extravasation.

The placebo injection will consist of 20 mL sterile 0.9% normal saline, delivered using the same technique. Both active and placebo injectates will be prepared by the unblinded scout nurse in unlabelled syringes of identical appearance to maintain blinding.

Following injection, transperineal prostate biopsy will proceed in the standard manner under general anaesthesia. The biopsy template and number of cores obtained will be determined by clinical factors.

Following the procedure, and prior to discharge, each patient will complete a VAS pain score form (Supplementary File S2). A clinical research team member will collect this form and record any additional analgesia administered post-operatively, on the same form.

Risks and Safety

PPNB is a well established and low risk adjunct to prostate biopsy. The most common adverse effects are pain and bruising at the injection site. Uncommon (1 in 1000) risks include nerve block failure, temporary numbness, allergic reaction to lignocaine, and iatrogenic injury to blood vessels, muscles or nerves. Very rare (1 in 10,000) complications include local anaesthetic systemic toxicity, seizures, or anaphylaxis. All injectates used in this study are approved for clinical use by the Therapeutic Goods Administration.

Patients may experience side effects or serious adverse events related to their TPPB, which will be managed as per clinical protocols and treated accordingly. Investigators will make records of any side effects or serious adverse events, as they are relevant to the scope of the study. This is in line with the NHMRC Safety Reporting and Monitoring in Clinical Trials (2016).

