### 2.8. Data Collection and Management

Baseline demographic and clinical data will be collected from medical records, including age, prostate volume (from pre-operative imaging), and previous prostate biopsies (number and type). Intra-operative data collected include number of cores and duration of procedure.

The primary outcome, post-procedure pain, will be assessed using a 10-point VAS score completed by participants prior to discharge. Secondary outcomes, including type and dose of post-operative analgesia, will be documented by the clinical research team and converted to oral morphine equivalents for analysis. Complications will be recorded prospectively during the admission and retrospectively through review of electronic medical records, with severity graded according to the Clavien–Dindo classification. This is summarised in Table 2.

All outcome data will be entered prospectively (coded) into a secure database hosted by Western Sydney Local Health District. Each participant will be assigned a unique study identification number, which will be used on all study forms and electronic entries. Identifiable information will be stored separately from coded data and accessible only to the principal investigators at each site. Access to the data is password protected and limited to only the named research investigators. Data will be retained for 15 years following study completion in accordance with local NHMRC Code for The Australian Code for the Responsible Conduct of Research. At the end of the retention period, electronic records will be permanently deleted and paper records securely destroyed.

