### 2.9. Statistical Analysis Plan

Descriptive statistics will be presented on baseline characteristics of the two groups. Continuous variables reported as mean (standard deviation) or median (interquartile range), while categorical variables will be reported as frequencies and percentages.

The primary outcome, post-operative pain measured by VAS, will be compared between groups using an independent-samples *t*-test if normally distributed, or a Mann–Whitney U test if non-normally distributed.

Secondary outcomes will be analysed as follows:Post-operative analgesia requirements (oral morphine equivalents) will be compared using *t*-tests or Mann–Whitney U tests, depending on data distribution.Complication rates will be compared between groups using χ^2^ tests or Fisher’s exact tests where appropriate.Procedure duration and number of biopsy cores will be analysed using *t*-tests or non-parametric equivalents.

All statistical tests will be two-sided, with a significance level set at *p* < 0.05. Effect sizes with 95% confidence intervals will be reported for primary and secondary outcomes. Missing data will be handled using complete case analysis. Statistical analysis will be performed using SPSS (Version 29, Armonk, NY, USA).

In the event of significant missing data, a sensitivity analysis will be performed to assess the robustness of these findings.

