### 3.1. Strengths

This multicentre, double-blinded, randomised controlled design is a key methodological strength, minimising selection and detection bias. Stratified randomisation by site also reduces site-specific confounding. The use of concealed allocations preserves the blinding of patients, surgeons, anaesthetists and outcome assessors. The protocolised PPNB technique and standardised outcome measurement strengthens the study’s reproducibility. Objective endpoints are achieved via standard conversion to oral morphine equivalents. The pragmatic inclusion of three tertiary centres also further strengthens the external validity within Australia.

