## Figures and Tables

**Table 1 cancers-18-01251-t001:** SPIRIT format of the study design.

Study Activities	Initial Consultation	Visit 1 (Day of Biopsy)
Informed consent	✓	
Inclusion/Exclusion Criteria	✓	
Physical examination	✓	
Baseline data collection and Randomisation		✓
Transperineal prostate biopsy ± periprostatic nerve block		✓
Post-operative pain questionnaire		✓

**Table 2 cancers-18-01251-t002:** Data collection per patient.

Domain	Variable	Definition	Source
Baseline	Age	Years at biopsy	Medical record
	PSA	Most recent PSA	Medical record
	Prostate volume	mL on MRI	Imaging
	Prior biopsy	Number and type	Medical record
Intra-operative	Procedure duration	Minutes	Operative note
	Cores taken	Number of cores	Operative note
Primary outcome	Post-op pain	VAS (0–10)	Patient survey
Secondary outcome	Analgesia use	Oral morphine equivalent (mg)	Medication chart
	Complications	Clavien–Dindo classification	Medical record review

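### The analgesia endpoint is analysed only as oral morphine equivalents, so it measures opioid consumption rather than the analgesia requirement named in the secondary objective

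*Protocol article*

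**What the plan says.** Section 2.1 of the protocol article sets a secondary objective: "to assess whether it reduces the requirement for post-operative analgesia". It does not restrict the kind of analgesic.

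Collection is equally broad. Under section 2.5 a research team member will "record any additional analgesia administered post-operatively, on the same form". Section 2.6 defines the endpoint as "Post-operative analgesia requirements, recorded as type, route, and dose, converted to oral morphine" equivalent.

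Analysis is narrower. Section 2.8 says that type and dose "will be documented by the clinical research team and converted to oral morphine equivalents for analysis". Section 2.9 states the test: "Post-operative analgesia requirements (oral morphine equivalents) will be compared using" t-tests or Mann–Whitney U tests, depending on distribution. Table 2 lists one analgesia variable, in milligrams of oral morphine equivalent. Section 3.1 counts this as a strength: "Objective endpoints are achieved via standard conversion to oral morphine equivalents".

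The article does not confine the endpoint to opioids, say how a drug without a morphine equivalent is scored, or plan a comparison of any analgesic use.

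**The concern.** The objective asks about analgesia, while the analysed variable can register only opioids. Paracetamol and anti-inflammatory drugs have no morphine equivalent, so they either add 0 mg or cannot be converted. A man who needed two non-opioid drugs and a man who needed none then have the same value.

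If the block mainly spares non-opioid drugs, the planned comparison would show little or no difference, and that could be reported as no effect on analgesic need. Section 4 says that a null finding would suggest the injection is unnecessary, so a null analgesia result caused by the scale could be cited in support. The reverse error is also possible: a fall in opioid milligrams could be reported as a fall in overall analgesic need when non-opioid drugs had simply taken their place.

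**Working it through.** **1. The plan's own figures.** The plan states no figure for this endpoint. Its only calculation is for the VAS: n per group = 2 × (1.96 + 0.84)² × (1.75 / 1.5)² = 2 × 7.84 × 1.361 = 21.3, rounded up to 22, with 50 recruited (25 per group). This reproduces and does not depend on the analgesia endpoint.

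**2. The sections side by side.**

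| Element | Where | Scope |
|---|---|---|
| Objective | 2.1 | Post-operative analgesia, any type |
| Recording | 2.5, 2.6 | Any additional analgesia, by type, route and dose |
| Analysis variable | 2.6, 2.8, Table 2 | Oral morphine equivalent |
| Test | 2.9 | t-test or Mann–Whitney on oral morphine equivalent |

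The scope narrows between recording and analysis. The information is collected and then left out of the tested variable.

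**3. What the narrowing could cost (illustration).** The documents give no rates of analgesic use, so every input here except the 25 per arm is an assumption.

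- 25 per arm, no missing data.
- Probability of any analgesic: p = 0.50 on placebo, 0.20 on block.
- A share f of users in each arm receives an opioid, so the probability of a non-zero value is p × f.
- Opioid doses are 5 to 15 mg; everyone else scores 0.
- The share of zeros over both arms is 1 − f × (0.50 + 0.20) / 2 = 1 − 0.35f.
- Two-sided 5% level; power of Mann–Whitney by simulation, of Fisher's test by exact summation.

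| Opioid share f | Opioid users, placebo v block | Zeros | Mann–Whitney on mg | Fisher on any analgesic |
|---|---|---|---|---|
| 1 | 50% v 20% | 65% | about 58% | 51% |
| 0.5 | 25% v 10% | 82.5% | about 27% | 51% |
| 0.25 | 12.5% v 5% | 91% | about 12% to 14% | 51% |

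The range in the last row reflects different simulation runs and dose assumptions.

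**4. Other assumed rates.** At 50% v 10%, the Mann–Whitney test has about 90%, 54% and 23% power at f = 1, 0.5 and 0.25, against about 83% for Fisher on any analgesic. At 40% v 16%, it has about 47% at f = 1 and 10% at f = 0.25, against 35%. The pattern is the same. The milligram test is somewhat stronger when all users receive opioids and much weaker when few do.

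**The case against.** The strongest reply is that oral morphine equivalents are a conventional measure of opioid sparing, that the data are kept, and that handling of drugs without a conversion factor belongs in an analysis plan that is not shown. Part of this stands. The milligram measure is legitimate and keeps dose. Non-opioid use is recorded and recoverable, so a reader who infers that the trial cannot see it goes too far: only the tested summary omits it. The appeal to an unseen plan is weaker, because the article itself fixes the variable and the test, and an analysis plan that followed it would inherit the mismatch.

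Other stronger readings are not supported:

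- **Power falls almost to nothing.** Fisher's test on opioid yes/no at 12.5% v 5% has only about 3% power, but section 2.9 does not plan that test. Under the planned Mann–Whitney test the figure is about 12% to 14%.
- **Most values will be zero because few men receive opioids.** The article names no non-opioid drug and gives no opioid share. If all users receive opioids, the planned test does slightly better than the yes/no test (58% v 51%).
- **The yes/no measure should replace milligrams.** It would treat one simple dose like repeated opioid doses and tell us nothing if non-opioids are routine.
- **Leaving out intra-operative opioid is part of the defect.** Objective and endpoint are both explicitly post-operative, so nothing is contradicted. That anaesthetists would give controls more opioid is conjecture.

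Section 3.2 concedes limited ability to detect smaller differences in secondary outcomes. That concerns sample size and does not cover a variable narrower than its objective.

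**Conclusion.** The point holds as a mismatch between objective and analysed variable. The article asks about analgesia of any type, records any type, and tests opioid milligrams alone. This follows from the text and from the definition of a morphine equivalent, and needs no assumed rate.

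Its practical size is unknown. Under the assumptions shown for 50% v 20%, power of the planned test runs from about 58% to about 12% to 14% as the opioid share among users falls from all to a quarter. If nearly all analgesia is opioid, little is lost beyond an imprecise label. If most is non-opioid, the planned comparison says almost nothing about the stated objective. This is a modest point about one secondary endpoint, worth correcting because correction is cheap.

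**What to change.** 1. In sections 2.6, 2.8, 2.9 and Table 2, name the oral-morphine-equivalent variable post-operative opioid consumption, state that non-opioid drugs do not enter it, and keep its planned test. Adjust section 3.1 to match.
2. Alongside it, pre-specify the proportion receiving any post-operative analgesic before discharge, with the risk difference and 95% CI. This is the comparison that answers the objective in section 2.1.
3. Tabulate non-opioid use by class and arm.

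All of this uses the type, route and dose already recorded, so no new data collection is needed. It should be fixed before unblinding; added later, it would be post hoc.

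The cost is one more secondary comparison. The yes/no measure ignores dose, and it is uninformative if non-opioids are given routinely. It will also be imprecise: at 50% v 20% with 25 per arm, the standard error of the risk difference is √(0.25/25 + 0.16/25) = 0.128, so the 95% interval is about 30 ± 25 percentage points. It should therefore be read as an estimate beside the milligram result.

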### 2.7. Sample Size

The primary outcome of interest is the between-group difference in the post-procedure VAS scores between the intervention (PPNB) and placebo injection. A meta-analysis of transrectal prostate biopsies demonstrated that PPNB was associated with a considerable reduction in post-procedural pain, with a pooled standardised mean difference of −1.27 (95% CI −1.72 to −0.82) compared with placebo [14]. Although this suggests a large effect size, the analysis also reported significant heterogeneity (I^2^ = 92%), reflecting variability across trials. A separate review of acute pain interventions reported that the minimum clinically important difference ranged from 0.4 to 4.0, with a median of 1.7 on a 10-point VAS [15].

On this basis, the sample size calculation assumed a between-group difference of 1.5 on the VAS, with a pooled standard deviation of 1.75, corresponding to a large effect size (Cohen’s *d* = 0.86). Using a two-sided α of 0.05 and 80% power, the required sample size is 22 patients per group. Allowing for dropout, a total of 50 patients will be recruited (25 per group). The sample size calculation was performed using G*Power v3.1.9.6 [16].

### 2.8. Data Collection and Management

Baseline demographic and clinical data will be collected from medical records, including age, prostate volume (from pre-operative imaging), and previous prostate biopsies (number and type). Intra-operative data collected include number of cores and duration of procedure.

The primary outcome, post-procedure pain, will be assessed using a 10-point VAS score completed by participants prior to discharge. Secondary outcomes, including type and dose of post-operative analgesia, will be documented by the clinical research team and converted to oral morphine equivalents for analysis. Complications will be recorded prospectively during the admission and retrospectively through review of electronic medical records, with severity graded according to the Clavien–Dindo classification. This is summarised in Table 2.

All outcome data will be entered prospectively (coded) into a secure database hosted by Western Sydney Local Health District. Each participant will be assigned a unique study identification number, which will be used on all study forms and electronic entries. Identifiable information will be stored separately from coded data and accessible only to the principal investigators at each site. Access to the data is password protected and limited to only the named research investigators. Data will be retained for 15 years following study completion in accordance with local NHMRC Code for The Australian Code for the Responsible Conduct of Research. At the end of the retention period, electronic records will be permanently deleted and paper records securely destroyed.

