### 2.4. Randomisation

After informed consent, participants will be randomised in a 1:1 ratio to receive either:

Intervention group: PPNB administered with 20 mL 1% lignocaine with 1:100,000 adrenaline (approved for use by the Therapeutic Goods Administration and listed on the Australian register of Therapeutic Goods (ARTG). The ARTG is a register of therapeutic goods that can be lawfully supplied in Australia), injected under ultrasound guidance immediately prior to biopsyControl group: placebo injection with 20 mL sterile 0.9% normal saline, injected under ultrasound guidance immediately prior to biopsy

The randomisation sequence will be computer generated using variable block sizes (2, 4 and 6); stratification will be by site. The allocation sequence will be prepared off-site by a trained study secretary, who will sequentially number and seal opaque envelopes. A box containing the required number of envelopes for use at each site will be made.

On the day of biopsy, a trained scout nurse will remove a sealed envelope from the box outside the operating theatre. The envelope will be opened, and the allocated injectate (PPNB or placebo) will be prepared in an unlabelled syringe of identical appearance. The scout nurse, who is not involved in outcome collection, will remain the only unblinded team member. Patients, surgeons, anaesthetists, and research staff collecting outcome data and performing analysis will remain blinded to allocation.

To reduce error, each envelope box will also contain a randomisation record, to be completed by the scout nurse at each location (Supplementary File S1). This document includes patient details, allocation, and solution preparation instructions, and will remain secured within the envelope box. A flowchart of instructions will also be affixed to each box to support adherence to protocol.

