These findings underscore that biopsy outcomes, such as patient-reported pain, may be influenced by operator-dependent factors such as experience, technical familiarity, and institutional practice patterns. Some degree of inter-operator and inter-centre variability is unavoidable and reflects pragmatic, real-world practice. In Australia, however, TPPB under general anaesthesia is the common and preferred approach. Thus, both trainees and consultant urologists in this study would have substantial exposure to and familiarity with the procedure, reducing the degree of operator variability compared to international settings where TPPB adoption remains inconsistent. Importantly, this enhances the external validity of the findings, although it may introduce additional variability in patient-reported outcomes.

Nevertheless, to date there is no high-quality evidence from randomised, double-blind, controlled trials examining PPNB (versus placebo) during TPPB under general anaesthesia. This multicentre trial is designed to address this evidence gap by providing blinded, controlled data on the effect of PPNB on early post-operative pain, analgesic use, and safety outcomes. However, the biggest challenge of this trial is that patient-reported pain is inherently subjective and may be influenced by individual pain thresholds, expectations, and peri-operative anxiety. Heterogeneity may also be introduced by the differences between centres in small variations in biopsy techniques.

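### No pre-operative pain score is collected, so variation in the discharge VAS from existing pain cannot be adjusted for; a baseline VAS used as a covariate is a cheap gain in precision

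*Protocol article*

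**What the plan says.** **Eligibility (section 2.2).** Any adult man booked for transperineal biopsy under general anaesthesia who can consent may enter. The only exclusion related to analgesia is a locoregional block in the previous 24 hours. Chronic pain and regular analgesic use are not mentioned.

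**Baseline data (section 2.8, Tables 1 and 2).** The text gives the variables as "including age, prostate volume (from pre-operative imaging), and previous prostate biopsies (number and type", and Table 2 adds PSA. None of these measures pain. Table 1 has a Visit 1 row for "Baseline data collection and Randomisation", but the only pain questionnaire in that schedule is post-operative.

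**Primary endpoint (section 2.6).** Pain is "measured using a 10-point visual analogue scale completed by the participant prior to discharge following TPPB", about 3–4 hours after anaesthesia. There is one score per man.

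**Primary analysis (section 2.9).** The two groups are compared by an independent-samples t-test or a Mann–Whitney U test, chosen by whether the scores look normal. There is no covariate.

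**Sample size (section 2.7).** The calculation "assumed a between-group difference of 1.5 on the VAS, with a pooled standard deviation of 1.75". It continues: "Using a two-sided α of 0.05 and 80% power, the required sample size is 22 patients per group". Then: "Allowing for dropout, a total of 50 patients will be recruited (25 per group".

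**The concern.** A man's pain before the procedure is a natural candidate predictor of his pain a few hours after it. If some men arrive in pain, part of the spread in the discharge VAS reflects how they came in. With about 25 men per group, such men may also fall unevenly between the arms by chance. An unadjusted test leaves both in the error term.

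Most refinements of an analysis can be settled in a later analysis plan. This one cannot, because a covariate that was never measured cannot be added. The decision has to be made at data collection.

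What is at stake is the width of the confidence interval for the primary difference and the power to detect 1.5 points. Validity is not in question: allocation is random, concealed and blinded, so existing pain has the same expected distribution in both arms.

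**Working it through.** **Inputs from the documents.** Difference 1.5, SD 1.75, two-sided alpha 0.05, power 80%, 22 per group and 50 in total (section 2.7); 1:1 allocation (section 2.4).

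**Step 1: reproduce the plan's figure.** Normal approximation: n per group = 2(1.960 + 0.842)² × 1.75² / 1.5² = 2 × 7.85 × 3.0625 / 2.25 ≈ 21.4, rounded up to 22. This matches. The exact t-test at 22 per group has non-centrality 1.5 / (1.75 × √(2/22)) = 1.5 / 0.528 = 2.84 on 42 degrees of freedom, which gives 79.3% power; 23 per group is needed to pass 80%. The difference of one man is not an issue. Recruitment is also consistent: 22 / 25 = 0.88, an allowance of 12% for dropout. With all 25 per group analysed, power is 84.4%.

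**Step 2: what SD 1.75 stands for.** Section 2.7 applies it to post-procedure VAS scores, which is the outcome as measured. On that reading it already contains whatever existing pain the men carry, so it is the total SD.

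**Step 3: the effect of a baseline covariate.** If baseline and discharge VAS correlate r within groups, the residual SD is 1.75 × √(1 − r²), and the standard error at 22 per group is that SD × √(2/22). The documents give no r, so the values below are assumptions.

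| r | Residual SD | Standard error | Power at 22 per group | n per group for 80% |
|---|---|---|---|---|
| 0 (no adjustment) | 1.750 | 0.528 | 79.3% | 23 |
| 0.2 | 1.715 | 0.517 | 80.9% | 22 |
| 0.3 | 1.669 | 0.503 | 82.9% | 21 |
| 0.5 | 1.516 | 0.457 | 89.4% | 18 |

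Residual variance falls by r²: 4%, 9% and 25%.

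**Step 4: the worst case for the change.** If r = 0, the covariate explains nothing and costs one degree of freedom (42 to 41). Power goes from 79.31% to 79.27%.

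**The case against.** **The plan contains no error here.** It has no contradiction and no wrong figure on this point, and randomisation protects the comparison. That stands, and it limits the point to an improvement in precision.

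**The gain may be negligible.** If few men have pain beforehand, r is small; at r = 0.3 the gain is under 4 percentage points. That also stands. The argument for acting is that the cost is smaller still.

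**A reader might infer that existing pain pushes power well below 79%.** Suppose a fraction q of men carry m extra points on top of SD 1.75, so that the SD becomes √(1.75² + q(1 − q)m²). Then q = 2% with m = 3 gives SD 1.80 and 77% power, and q = 10% with m = 5 gives SD 2.30 and 56%. Those figures hold only if 1.75 excludes existing pain. The documents do not say so, and section 2.7 points the other way; neither q nor m is given anywhere. The figures must not be set beside the gains in the table, which rest on the opposite premise.

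**A reader might infer that a man who arrives at 5 and leaves at 5 is counted as having 5 points of biopsy pain.** That depends on the wording of the VAS form, Supplementary File S2, which is not shown. If it asks about pain from the biopsy only, the example weakens.

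**A reader might infer that the protocol names this very problem.** Section 3 says that "the biggest challenge of this trial is that patient-reported pain is inherently subjective and may be influenced by individual pain thresholds, expectations, and peri-operative anxiety". Thresholds, expectations and anxiety are not existing pain, and a baseline VAS measures none of them.

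**A reader might infer that an imbalance could never be seen.** Screening reviews medical history (section 2.3) and baseline data come from medical records (section 2.8). Known chronic pain or regular analgesics could therefore be partly recovered. What is lost for good is the same-day score on the outcome's own scale.

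**Conclusion.** The point holds as an inexpensive improvement in precision. The documents confirm that men with existing pain are eligible, that no pre-operative pain score is listed, and that the single discharge VAS is compared without adjustment. The word that opens the list in section 2.8 leaves it open-ended, but the per-patient data table and the schedule show no such score either.

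With 1.75 as the total SD, adjustment would move power at 22 per group from 79.3% to about 81–89% for r between 0.2 and 0.5. It would do almost nothing if nearly all men start at 0. The value of r is an assumption throughout.

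The documents do not support a claim of bias, nor a claim that power is really 56–77%. The latter applies only if 1.75 is assumed to leave out existing pain.

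**What to change.** 1. At Visit 1, before anaesthesia and before the envelope is opened, have each man complete the same 0–10 VAS. Add it to the baseline rows of Table 2 and to the schedule in Table 1.
2. In section 2.9, make the primary estimate the between-group difference in discharge VAS, with its 95% confidence interval, from a linear model with baseline VAS as covariate. This replaces the choice between t-test and Mann–Whitney test according to the observed distribution. It also keeps the analysis on the mean difference that section 2.7 was sized to detect.
3. Because section 2.9 handles missing data by complete cases, state that a missing baseline score does not remove a man from the primary model (for example, by setting it to the overall baseline mean).
4. Optionally, record regular analgesic use (yes/no) as a descriptive item. It would help in reading the oral-morphine-equivalent endpoint and needs no place in the primary model.

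Eligibility stays as it is. The cost is one form item per man and one degree of freedom, with no added visit, procedure or participants. The score cannot be obtained after the biopsy, so the change has to be in place before a man's procedure to be of use for him.
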